**Figure 1 Fig1:**
[figure not shown]
**RaDIANT community study flow diagram for dialysis facility selection.**

Table 1 reports the characteristics of all dialysis facilities in Georgia (n = 283) and compares characteristics of the pool of dialysis facilities selected for potential randomization (*i.e*., meeting the two-tiered selection criteria) vs. facilities not selected for potential randomization. A greater proportion of patients within facilities selected for the RaDIANT Community study (vs. the facilities not selected) have higher proportions of AA (65.4% vs. 49.0%) patients compared to GA dialysis facilities not selected for the study. Dialysis facilities selected for the RaDIANT Community Study also have a higher proportion of patients with Medicaid insurance only (11.0% vs. 8.5%), patients who are unemployed (70.0% vs. 64.1%), and patients who have hypertension (91.4% vs. 88.1%) compared to facilities not selected for the study (p < 0.05 for each). As expected, facilities included in the RaDIANT Community Study have lower likelihood of placement on the national deceased donor waiting list and kidney transplant rates, compared to facilities that were not selected for randomization (Table 1).

**Table 1 Tab1:** **Baseline characteristics of dialysis facilities, comparing all dialysis facilities in Georgia, the facilities selected for randomization, and dialysis facilities not selected for randomization**

Facility characteristic	Dialysis facilities in Georgia (n = 283)	Pool of dialysis facilities randomized for intervention (n = 134)	Remaining dialysis facilities in Georgia not selected for randomization (n = 149)	p-value
**Facility Demographic and Clinical Characteristics**				
# Patients per Facility, Mean, SD	46.0 ± 25.7	46.6 ± 25.5	45.4 ± 26.0	0.57
Number of Staff, Mean, SD	10.0 ± 7.4	10.1 ± 6.5	9.8 ± 8.1	0.48
For Profit, %	90.3	88.7	88.3	0.91
Average Age, Mean, SD	61.4 ± 5.9	61.2 ± 5.7	61.6 ± 6.1	0.76
% White	40.9	33.5	46.8	<0.001
% African American	56.5	65.4	49.0	<0.0001
% Uninsured	12.2	11.5	12.6	0.51
% Medicaid Only	9.1	11.0	8.5	0.01
% Unemployed	67.1	70.9	64.1	0.06
Time on Dialysis (Years), Mean, SD	4.9 ± 1.8	5.0 ± 1.21	4.8 ± 1.1	0.32
% Receiving No Access to Pre-ESRD Nephrology Care	27.3	26.0	28.3	0.28
% Not Informed of Transplant Options	2.8	3.1	2.4	0.28
% Diabetes	59.9	59.9	59.0	0.51
% Hypertensive	89.6	91.4	88.1	0.02
% AV Fistula	13.1	13.8	12.3	0.49
% of Incident Patients with AV Fistula	29.7	28.7	30.5	0.46
Average Count of Comorbidities, Mean, SD	3.0 ± 0.8	3.0 ± 0.8	2.9 ± 0.9	0.30
% ESA Prior to Dialysis	17.6	18.0	18.0	0.25
Standardized Mortality Ratio	1.06	1.07	1.05	0.41
**Transplant Access Measures at Baseline**				
% Waitlisted (Age < 70 yrs only)	17.8	15.5	20.4	<0.0001
Standardized Transplantation Ratio (2008–2011)	0.56	0.46	0.68	<0.001

### Study aims & objectives

The primary aim of the RaDIANT Community Study is to improve referral for kidney transplantation among AA ESRD patients in GA (primary outcome change in 1-year facility-level referral rate between intervention and control facilities). The secondary aim of the RaDIANT Community Study is to evaluate whether the implementation of this intervention reduced racial disparities in kidney transplant referral within and beyond the RaDIANT Community Study.

### Transplant referral data collection

The SEKTC recognized that a major gap in our knowledge of transplant disparities was the limited data available on patient- or facility-level referral for medical evaluation at a kidney transplant center, a key step in access to transplantation. Through our Coalition partners, we had the unique ability to access data on kidney transplant referrals from the transplant centers in the tri-state region. As this was the largest collection of transplant referral data collection to our knowledge, and because our data suggested that GA had the lowest kidney transplant rates, we chose to start tri-state data collection among the three adult transplant centers in GA: Emory Transplant Center (Atlanta, GA), Georgia Regents Kidney and Pancreas Transplant Program (Augusta, GA), and Piedmont Transplant Institute (Atlanta, GA). To ensure consistency of defining referrals, our Coalition partners – ESRD Network 6 – hosted several conference calls with CMS and other ESRD Networks that were collecting transplant referral data as part of the ESRD Network Statement of Work and Pilot Innovation projects. Partners agreed to define referral as when the transplant center received the patient’s referral form at the transplant center. The patient-level data collected from each transplant center included patient age, race/ethnicity, date of dialysis start, and date of transplant referral, evaluation, and waitlisting. Referral date was defined as the date in which the transplant center received a faxed transplant referral form from a dialysis facility or referring provider. Each transplant center securely sent patient-level referral data to ESRD Network 6, which served as the data coordinating center. ESRD Network 6 linked patient-level referral data with dialysis facility data by unique provider number using CROWNWeb. CROWNWeb is a web-based reporting system that allows dialysis facilities to report patient data. Following linkage with CROWNWeb, deidentified patient data were then linked to dialysis facility-level demographics using the publicly available 2012 Dialysis Facility Report data.

### Standard-of-care intervention (Study arm 1)

Dialysis facilities randomized to the standard-of-care intervention did not receive any specific quality improvement interventions related to transplant education. By law, all dialysis facilities are required to educate patients about transplantation as a treatment option and record the assessment of this in the patient’s Medicare eligibility (CMS-2728) form, although the quantity and quality of this education is unknown and may vary from facility to facility.

### Multicomponent intervention (Study arm 2)

Based on the results of the population needs assessment, the SEKTC aimed to develop a sustainable, multicomponent, multi-level quality improvement intervention to address disparities at the dialysis facility-, staff- and patient-level. These intervention activities were developed (or identified) by SEKTC members in face-to-face and phone conference meetings over several months. Final intervention activities were selected by the SEKTC Steering Committee members based on 1) feasibility, 2) sustainability, 3) core tenets of quality improvement interventions, and 4) perception of acceptance among stakeholders, including dialysis facilities, staff, and patients, as well as the larger kidney disease community.

The multicomponent, multi-level, quality improvement intervention targeted to dialysis facilities, staff, and patients includes educational webinars, staff- and patient-level educational activities, monthly monitoring of quality improvement activities, and traditional quality improvement oversight. Because ESRD Network 6 has significant experience with conducting large quality improvement interventions within dialysis facilities that may be performing worse than expected for a particular outcome, and because disparity reduction in transplant referral is part of the CMS Statement of Work for ESRD Networks [48], intervention activities are primarily delivered by ESRD Network 6. The ESRD Network retains the authority to mandate facility participation in quality improvement activities if deemed to have low performance; thus interventions are targeted to dialysis facilities that had either low overall kidney transplant referrals or those facilities that had a racial disparity within their facility (*i.e*., they had a lower proportion of AA vs. whites referred for kidney transplantation).

Intervention activities are designed to target and span multiple levels, including patient, facility staff, and facility protocol levels (Figure 2). For example, there are several interventions that target facility policies and protocols, including the requirement that facilities create their own transplant referral quality improvement plan by journaling their goals, obstacles, and successes; working with the ESRD Network on quality improvement assistance and review; creating a patient and family advisory group; conducting a transplant education month; hosting a movie night including culturally sensitive information about living donation; and establishing a peer mentoring program to help facilitate transplant recipients to speak to potential transplant candidates. In addition, facilities must report their monthly referrals to ESRD Network 6 and are given a baseline and mid-year report on their own facility’s performance related to transplant referral. Facility staff are recommended to attend their own facility’s kick off quality improvement session on improving transplant referrals, attend monthly educational webinars developed by SEKTC members, attend a transplant educational seminar or session across the state (including “Trends in Transplant” hosted by the Georgia Transplant Foundation, or Explore Transplant), and complete an online patient safety module. Educational activities targeting patients within facilities include bulletin boards that facility staff must set up to educate patients about transplantation, the opportunity to participate in the patient and family advisory group for transplantation, and the receipt of a patient educational “toolkit” about transplantation. The major intervention activities are described in more detail below.

**Figure 2 Fig2:**
[figure not shown]
**Description of patient-, staff-, and facility-level interventions for RaDIANT community study.**

### Educational webinars

ESRD Network 6 and various SEKTC members will host monthly webinars (45- to 55-minute internet educational seminars), which are intended to serve as a platform for all parties to discuss potential barriers to kidney transplantation, brainstorm ideas to overcome these obstacles, and celebrate successes. Webinars will cover the following topics: transplant quality improvement project overview, review of facility-level baseline transplant referral data feedback reports, how to establish a patient mentoring program, education materials for facility staff and patients, including Explore Transplant [49] and a shared patient/provider web- and mobile-based decision aid (iChoose Kidney; described below) that provides individualized mortality risks comparing dialysis vs. transplantation treatments that was co-developed by SEKTC partners, and a culturally sensitive DVD targeting the AA community [(Living About Choices in Transplantation and Sharing (ACTS) [50, 51]] detailing the advantages of LD kidney transplantation, financial issues related to transplantation, a question & answer discussion with transplant center outreach coordinators, a session on how staff can give patients an “elevator pitch” about kidney transplantation, a question & answer discussion with a transplant center medical director, and a “Patient’s Voice” session, during which transplant recipients talk about their personal experiences. Email reminders for webinar topics will be emailed to the dialysis facility project lead and project lead alternate staff member. Participation will be verified for each dialysis facility using a live check-in system; recorded webinars will be available following the live session.

### Patient and family educational programs

Implementation of patient and family education programs will be required at each dialysis facility in order to help inform individuals on the benefits of transplantation and information about how to navigate the transplant process. Along with dialysis facility-specific education programs, each facility will be provided with Living ACTS DVD and an electronic version of the Living ACTS booklet that could be printed and dispensed to patients and their family and help improve their knowledge of kidney transplant and the benefit of living donation. These materials are specifically designed for the AA community [51]. Dialysis facilities will also be encouraged to either develop a mentoring program that will connect patients and their families to former transplant patients, or utilize the Georgia Transplant Foundation’s (GTF) established program (the Dialysis Liaison Program) to match transplant recipients with dialysis patients within a facility [52]. SEKTC members developed a “peer mentoring toolkit” for facilities to provide recommendations for how mentors should be utilized within the facility to help improve access to kidney transplantation. A SEKTC partner, Georgia Transplant Foundation, will aid in tracking utilization of peer mentors at the facility level.

### Transplant referral data reports

Similar to previous quality improvement interventions in ESRD Network 6 [47, 53–55], facilities will receive a baseline and mid-year facility-specific quality-of-care feedback report detailing their individual facility’s referral for kidney transplantation, including the overall proportion of patients referred as well as the proportion of white vs. AA patients referred, based on data reported from the three transplant centers in GA. The feedback reports also detail information about low kidney transplant rates and racial disparities in the average time from dialysis start to referral for ESRD patients in GA (Figure 3).

**Figure 3 Fig3:**
[figure not shown]
**Example kidney transplant referral feedback report for dialysis facilities.**

### Monthly monitoring of transplant referral data

Similar to previous dialysis facility quality improvement activities, ESRD Network 6 is responsible for monthly monitoring of the intervention facilities. Facilities will be required to submit a monthly report of the status of each patient in their facility, including whether the patient has been referred for kidney transplantation, and if so, whether they have been evaluated by the transplant center, waitlisted, or received a transplant. If the patient has not been referred, facilities must document the reason. At one year following the intervention, transplant centers will also report patient-level referral data to validate the monthly, facility-reported referral data and conduct the outcome evaluation.

### Quality improvement assistance and review

Dialysis facility-specific action plans to reduce disparities and to improve access to kidney transplant referrals will be a required component of this multicomponent intervention. Facility staff will receive detailed information (via email) about the core elements of quality improvement, including how to conduct a root cause analysis and identify a list of potential barriers. ESRD Network staff members will provide assistance and review of facility-specific action plans.

### Facility leadership and staff-level interventions

At baseline, dialysis facility staff members will be required to attend an informal orientation reiterating the importance of transplant. Dialysis facility leadership will be instructed by the ESRD Network staff members to host the orientation in order to provide details about the quality improvement project, but each facility has the flexibility for how and when they communicate the information to the facility staff. The orientation allows the facility to communicate with staff and show their dedication to improving referral rates, which can ultimately impact patient outcomes. To emphasize the commitment to improving transplant referrals, staff members will be encouraged to participate in Georgia Transplant Foundation’s symposium on “Trends in Transplant”—a free, educational conference that joins transplant physicians with potential candidates.

### Patient-level interventions

Facilities will be required to form Patient and Family Advisory Groups that are focused on increasing transplant referral. The Advisory Group is recommended to hold regular meetings to discuss referral activities, educational programs, and patient outreach. Along with the Advisory Group, patients will be given the opportunity to collaborate with dialysis facility staff in the creation of a “Kidney Transplant Toolkit”. This toolkit will give other dialysis facility patients a comprehensive overview of the transplant process including where to go for transplant evaluation, common questions and answers about the transplant process, potential barriers, and lessons learned from transplant recipients. Various educational resources (that have been previously developed and are easily accessible online) are included in this toolkit, including evidence-based patient education materials. The iChoose Kidney website and mobile application (iPhone and iPad tool) is an educational tool available to patients and their health care staff which uses patient age, sex, race, time on dialysis, and comorbidities to predict an individualized risk of mortality if the patient were to remain on dialysis vs. to receive a kidney transplant. The tool presents relative and absolute risks both numerically and graphically, utilizing best practices for health communication [56].

### Outcome measures

The primary outcome of the RaDIANT Community Study is the change in facility-level transplant referral (for patients <70 years) from baseline. Baseline referral will be calculated as the average number of unique referrals in a dialysis facility over the 12-month period preceding the intervention (January-December 2013) divided by the total number of ESRD patients within the facility for that time period. Post-intervention crude referral will be measured as the average number of unique referrals generated from January-December 2014 divided by the total number of ESRD patients within the facility for the same 12 month intervention period. As described above, referral will be defined as the receipt of a referral by the transplant center. Patient-level transplant referral data with facility identifiers will be collected from all of the transplant centers in GA and aggregated to summarize the total number of referrals to any transplant center in the state divided by the total number of adult ESRD patients <70 years in the facility. If facility characteristics are not equally distributed at baseline between control and intervention groups, we will consider adjustment using a Standardized Transplantation Referral Ratio (STRR). The STRR will be defined as the total number of observed transplant referrals within a facility divided by the total number of expected referrals based on the state average and adjusting for relevant covariates, among patients aged 18–69 [similar to the Standardized Transplantation Ratio (STR) used by CMS] [1].

A secondary outcome of interest is the reduction in AA vs. white racial disparity in transplant referral. The reduction in racial disparity will be measured as the difference in the proportion of referrals among AA vs. whites. Furthermore, we will examine whether the total number of AA ESRD patients referred for transplant in the state of GA increased from baseline to 12 months to examine the absolute impact of the RaDIANT Community Study on improving access for AA ESRD patients in the state.

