### Target population, setting, and inclusion/exclusion criteria

Under the direction of Centers for Medicare & Medicaid Services (CMS), 18 regional ESRD Networks are responsible for the quality of care of patients with kidney disease in the US. ESRD Network 6 (GA, NC, and SC) has the largest ESRD patient population among the US ESRD Networks, servicing more than 600 dialysis facilities that treat ~40,000 patients. Approximately 47% of the dialysis facilities in ESRD Network 6 are located in GA, and these facilities treated more than 12,000 dialysis patients in 2012 [47]. The RaDIANT Community Study aims to target 134 outpatient dialysis facilities in GA, representing nearly half (47%) of all GA dialysis facilities.

All dialysis facilities within GA were considered for randomization of the intervention (n = 283). To ensure that each facility had a large enough population to detect a change in the main effect of disparity reduction, facilities with a 2012 population of <25 patients (18-69 years of age) were excluded from the potential pool of facilities (n = 11). The remaining facilities were selected in a step-wise selection process: 1) The presence of a racial disparity in transplant referral (n = 75), or 2) crude annual referral in the lowest 50th percentile (referral <0.06; n = 59) for the state. The presence of a racial disparity was based on a difference of the proportion of AA ESRD patients referred and the proportion of white ESRD patients referred. The remaining facilities selected had a calculated crude referral in the lower 50th percentile. The final pool of 134 facilities were randomized by generating a random number to either the intervention (n = 67) or control (n = 67) group (Figure 1). Dialysis facilities in the intervention group are not blinded to intervention activities; however, facilities selected as controls are blinded. Researchers are not blinded to dialysis facility allocation.

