### Statistical analyses

Descriptive analyses of facility-level baseline variables (demographic, clinical characteristics and transplant access measures) will be compared and differences between study arms at baseline will be evaluated using either *t* tests or their non-parametric equivalents for continuous variables and chi-square test for categorical variables. Significant differences in baseline characteristics will be adjusted when assessing the overall intervention effect as described above.

To evaluate the effect of the intervention on improvement in transplant referral by study arm, we will calculate the difference in facility-level transplant referral rate from baseline to 12 months for each facility in the study. Analysis of covariance (ANCOVA) will be used to test for post-intervention mean differences in referral rates for the control and intervention group after adjusting for the baseline referral rates and facility characteristics that differed significantly across the two arms at baseline. For skewed outcomes, differences in the intervention and control groups will be evaluated using a non-parametric Wilcoxon rank sum test.

For our secondary outcome, AA vs. white racial disparity in transplant referral, we will examine whether (i) the proportion of AA patients referred for transplantation increased from baseline to 12 month follow up at the facility level and (ii) whether there is a differential effect in the intervention group compared to the control group over time, after adjusting for between facility heterogeneity. A mixed effects model will be used to test for differences in the proportion of AA patients referred between baseline and 12-month follow up in the two study arms respectively. Fixed main effects of (a): time (measured in months from baseline; baseline assumed month 0) (b): intervention status (control = 0, intervention = 1), and (c) their interaction on referral disparity, averaged across different subpopulation of facilities will be assessed. Facility level random effects (intercepts and slopes) will be considered to adjust for variations in the average time trend due to unmeasured confounding independent of the intervention. If the individual facility trajectories indicate a similar time trend (slope), a random intercept only model will be sufficient to account for between facility heterogeneity at baseline.

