To examine the absolute increase of the intervention on AA ESRD patient referrals, patient-level logistic regression analysis will be performed with intervention status, race (AA versus whites) as primary independent variables and controlling for patient-level baseline characteristics. Because patients are clustered within facilities, we will adjust for the clustering effect. Interactions between intervention and race will be included to test for the differential intervention effects by race. For interpretation of findings, we will compare and contrast the standardized predicted referral rates by racial group within the intervention and control facilities, respectively.

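### The statewide before-after count of African American (AA) referrals is given as the study's absolute impact; that statement should rest on the randomized arms, with the count descriptive only

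*Protocol article*

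**What the plan says.** Three parts of the protocol article bear on this.

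- **Outcome measures.** After defining the disparity outcome, the article adds that it will "examine whether the total number of AA ESRD patients referred for transplant in the state of GA increased from baseline to 12 months". The stated purpose is "to examine the absolute impact of the RaDIANT Community Study on improving access for AA ESRD patients in the state".
- **Statistical analyses, secondary outcome.** Two questions are listed. Item (i) is whether "the proportion of AA patients referred for transplantation increased from baseline to 12 month follow up at the facility level". Item (ii) is whether "there is a differential effect in the intervention group compared to the control group over time". A mixed model with time, arm and their interaction serves both. For the AA absolute increase, the section then says that "patient-level logistic regression analysis will be performed with intervention status, race (AA versus whites) as primary independent variables", allowing for clustering, and that "Interactions between intervention and race will be included to test for the differential intervention effects by race".
- **Target population, setting, and inclusion/exclusion criteria.** The 134 randomized facilities were chosen in two steps. The first criterion was "The presence of a racial disparity in transplant referral" (75 facilities). The second was crude annual referral in the lower half of the state, below 0.06 (59 facilities). The year of the referral data used for selection is not given. The baseline window for outcomes is calendar 2013.

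**The concern.** The statewide count carries a causal label, but nothing in it separates the intervention from whatever else changed in Georgia between 2013 and 2014. Any general movement in referral practice, or any growth in the AA dialysis population, enters it in full. The article itself gives a reason to expect movement: the section on the multicomponent intervention notes that reducing referral disparity is part of the federal Statement of Work for ESRD Networks. A general decline would do the opposite and hide a real effect.

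Item (i) has a related weakness. It asks about change over time without reference to the control arm, in facilities chosen because referral was low or unequal. If the selection data and the baseline data overlap, part of that low value is chance and will not recur.

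At stake is a favourable statement about AA access that could be made even if the intervention did nothing, in a trial that has a randomized control arm.

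**Working it through.** **1. The plan's own figure.** Inputs from Power and sample size calculations: 67 facilities per arm, 46 patients each, 14% control referral, ICC 0.01 to 0.05. Effective n per arm = 67 × 46 / [1 + 45 × ICC].

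- ICC 0.01: 3,082 / 1.45 = 2,125.5. Two-sided 5% power for 3.1 points is 79.7%.
- ICC 0.05: 3,082 / 3.25 = 948.3. Power for 4.8 points is 80.6%.

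The stated 80% is reproduced, so 3.1 to 4.8 points is a fair yardstick.

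**2. Who is behind the statewide count.** Inputs from Table 1: 283 facilities, 46.0 patients each, 56.5% AA statewide; 46.6 patients and 65.4% AA in the randomized pool.

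- State: 283 × 46.0 × 0.565 = 7,355 AA patients.
- Intervention arm: 67 × 46.6 × 0.654 = 2,042.
- Share: 2,042 / 7,355 = 27.8%, so about 72% are outside intervention facilities.

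**3. What would mimic the design effect.**

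| | 3.1 points | 4.8 points |
|---|---|---|
| Extra AA referrals (effect × 2,042) | 63 | 98 |
| Equivalent statewide rise (÷ 7,355) | 0.86 points | 1.33 points |
| Equivalent growth in AA patients at 14% referral (÷ 1,030) | 6.1% | 9.5% |
| The same at 6% referral (÷ 441) | 14.3% | 22.2% |

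The article gives no AA-specific statewide referral rate. The 14% is the assumed control proportion and the 6% is the lower-half cut-off, so the last two rows show a range. The equivalent rise in points does not depend on that rate.

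With Poisson counts, the chance SD of the yearly change is √(2 × 1,030) = 45 at 14% and √(2 × 441) = 30 at 6%. Sixty-three extra referrals are then about 1.4 or 2.1 SD, so at 14% the count is also a weak signal.

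**4. Item (i) under no effect and no trend.** This was simulated with 272 facilities (283 − 11), 30 AA and 16 white patients each, beta-binomial facility rates and no true racial gap. The 75 largest disparities were selected, then the 59 lowest referral rates among the rest, and the pool was split at random.

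| Mean rate | ICC | Change in AA referral, intervention | Change, control |
|---|---|---|---|
| 6% | 0.01 | +2.58 | +2.57 |
| 6% | 0.05 | +2.08 | +2.09 |
| 10% | 0.01 | +3.43 | +3.42 |
| 10% | 0.05 | +2.65 | +2.64 |
| 14% | 0.01 | +3.92 | +3.90 |
| 14% | 0.05 | +3.13 | +3.16 |

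These are percentage points when selection used the baseline year itself. The arms differ by at most 0.03. If selection used an earlier, independent year, the change is about 0. Over all facilities in the state it is also about 0.

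**The case against.** The strongest reply is that the controlled analyses are already in the plan. Item (i) is half of a sentence whose other half, item (ii), compares the arms over time. The analysis named for the absolute increase in AA referrals is the patient-level model with arm, race and their interaction. The statewide count is introduced as an additional look, with no test or threshold, and Study aims & objectives declares an interest in disparity beyond the study, which a statewide figure can serve as description. All of this stands, and it limits the point to how two measures are interpreted.

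A reader might infer more, in three ways that the article does not support.

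- *That the plan ignores its control arm for AA referral.* Item (ii) and the logistic model both use it.
- *That selecting poorly performing facilities inflates the statewide count.* The count covers every Georgia facility, selected or not, so this form of regression to the mean does not reach it. Its weaknesses are trend, population growth and dilution.
- *That regression to the mean in item (i) is certain.* It needs overlap between the selection and baseline data. The article's figures even sit awkwardly with overlap: if 59 of 134 facilities were at or below 6% and the pool averaged 14% with equal weights, the other 75 would have to average at least (134 × 0.14 − 59 × 0.06) / 75 = 20%. That suggests different data or definitions but does not settle it.

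What the reply does not remove is the sentence in Outcome measures. It still ties absolute impact to the uncontrolled count, while Statistical analyses ties the absolute increase to a between-arm model. The two can disagree, and nothing says which governs.

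**Conclusion.** The point holds for the statewide count and, conditionally, for item (i) read alone. A drift of about 0.9 to 1.3 points across the state would look the same in the count as the full design effect in the intervention facilities. A within-arm rise of 2.1 to 3.9 points could appear in item (i) with no effect, but only if the selection data are the baseline data.

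The primary ANCOVA, item (ii) and the logistic model compare randomized arms, where trend and regression to the mean are expected to cancel. They are not in question. This is a should-fix correction to secondary outcomes.

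The size rests on treating Table 1 facility averages as patient-weighted, on taking its patients per facility as the relevant population under 70, and on the simulation assumptions listed. The lack of a comparator and denominator depends on none of these.

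**What to change.** - In Outcome measures, define absolute impact as the baseline-adjusted intervention-minus-control difference in the AA referral proportion, multiplied by the number of AA patients under 70 in the intervention facilities, with a confidence interval. At the design effect this would be about 63 to 98 referrals a year.
- Name one source for that difference. Either use the arm-by-time contrast in the mixed model, fitted to AA referral, or use the logistic model with the facility's baseline AA referral added.
- Report the statewide AA figure as description only: a rate with its denominator for each year, without the language of impact.
- Treat the item (i) changes the same way. Show both arms side by side and do not offer either as evidence of effect.
- State which year's referral data were used to select facilities. If it overlaps 2013, say that some within-arm improvement is expected by chance.

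The cost is wording and light analysis, since the data are already to be collected. The impact statement will be more modest than a raw statewide increase.
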